### Study setting

The study will be conducted in the antenatal clinics of five NSW hospitals of which three are rural (Orange Base, Lismore Base and Dubbo Base) and two metropolitan (Liverpool and Blacktown). Hospitals were recruited through an expression of interest process addressed to the general manager of each site in the first instance. Agreement was also obtained from the midwifery unit manager and obstetric lead of the maternity unit at each hospital to ensure local support prior to inclusion. All hospitals are public hospitals accounting for approximately 10 % of the total births in NSW and the demographic characteristics of women attending the two metropolitan and the three rural hospitals are similar within their categories. The hospitals offer a variety of antenatal care options for women including hospital-based, shared care with general practitioners or via community based midwifery group practices. All of these care models require women to attend the hospital for an initial antenatal appointment which usually occurs after 12 weeks of gestation.

### Recruitment strategies

Pregnant women who are presenting at one of the five participating hospitals will receive a flyer with their initial appointment letter and advised that their midwife will discuss the Get Healthy in Pregnancy service and research trial with them at their first appointment. Midwives during the recruitment period will screen and assess every woman presenting for their first antenatal visit to determine eligibility to be enrolled in the study. Women eligible to participate will be offered the opportunity to participate in the trial and asked for written consent. Women who are unsure whether they participate will be contacted by a research assistant within a week and reoffered the opportunity to participate.

### Participants

Participants will be 710 pregnant women who attend one of five hospitals during the recruitment period and are English speaking, 18 years and over, have a singleton pregnancy, have a gestation of 18 weeks or under and agree to participate (signed consent forms and verbal consent provided at first coaching call).

### Medical conditions

An exclusion list and requirements for medical clearance (Table 1) for women with conditions that may impact their involvement was established to ensure safety of the women participating in the study. The national guidelines for consultation and referral by midwives [32] were used to identify the medical conditions for exclusion or medical clearance. For the purpose of this study, all conditions identified within the guidance as requiring referral to a medical practitioner for specialist care were reviewed by the GHiP Expert Advisory Group with regard to the woman’s ability to be able to safely modify her diet or levels of activity.

**Table 1 Tab1:** Medical conditions for exclusion from the study or requiring clearance from a medical practitioner

	Pre-existing conditions (at screening)	Conditions developed during the study period
Excluded from the study	Cardiovascular disease: • Arrhythmia/palpitations; murmurs: recurrent, persistent or associated with other symptoms • Cardiac valve disease • Cardiac valve replacement • Cardiomyopathy • Congenital cardiac disease • Ischaemic heart disease • Pulmonary hypertension Endocrine: • Pre-existing Type 1 diabetes • Cystic fibrosis • Phenylketonuria (PKU) Respiratory Disease • Sarcoidosis Severe lung disorder	• Fetal death in utero • Small for dates (<10th centile) • Multiple pregnancy • Preterm birth (<36 weeks) • Rupture of membranes (<36 weeks) Placental indications: • Placental abruption • Placenta accrete • Placenta preavia • Vasa Praevia
Medical clearance required to participate	Cardiovascular disease • Hypertension Neurological • Epilepsy Respiratory disease • Asthma Moderate (women requiring daily bronchodilators and steroid inhalers) • Type 2 diabetes (diet/medication controlled) Skeletal problems • Musculo-skeletal problems Previous obstetric history • Previous pre-term birth • Recurrent miscarriage History of mental health • History of mental health conditions (e.g. eating disorders) Endocrine • Type 2 diabetes (diet/medication controlled) Gastro-intestinal Coeliac Disease	Endocrine • Pre-existing Type 2 diabetes now requiring medication Skeletal problems • Herniated vertebral disc • Symphysis pubis dysfunction Cardiovascular disease Chronic hypertension Obstetric related • Anaemia (Hb <90) • Fetal size small for dates • Vaginal blood loss • Pre-eclampsia • Gestational diabetes – diet/medication controlled Gestational hypertension

For women requiring medical clearance, the participant file will be forwarded to a medical practitioner for review. During the review the medical practitioner will be required to select from three options; clear the woman for full participation in the trial, exclude from the trial, or provide parameters within which the woman can participate (eg. restricting certain forms of physical activity or certain variations to the woman’s diet).

### Sample size

A total of 710 women will be recruited; 177 and 532 pregnant women with a pre-pregnancy BMI of 18.5–24.9 kg/m^2^ (healthy range) and ≥25.0 kg/m^2^ (overweight or obese range) respectively. 248 women will be recruited across the three rural hospitals with 462 recruited at metropolitan hospitals. The higher numbers in metropolitan hospitals is to reflect the larger target population in these areas.

The sample size has been calculated using previous reports of weight gain during pregnancy [10, 13, 33] to detect a difference of 3 kgs in gestational weight gain between intervention and control groups at 80 % power. Attrition rates of 60 % in the coaching arm and 30 % in the information only arm are expected. These rates account for the up to 15 % of women, across both arms, who start the study and go on to develop conditions during pregnancy that exclude them from further participation [34] and, allows for the perception of participant burden in the coaching arm. The relatively high attrition rate is conservative compared with other population based programs.

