## Methods/Design

### Aims and objectives

This study will compare the effectiveness of a telephone-based health coaching program versus provision of information alone in supporting pregnant women to achieve appropriate gestational weight gain. Pregnant women will be stratified into pre-pregnancy healthy weight and overweight/obese groups. Given the evidence around issues related to excessive weight gain in pregnancy, a pure control group was not included in the study as it was considered inappropriate to not provide information that could be beneficial to maternal and neonatal health.

The hypothesis of the study is that, pregnant women enrolled in the coaching program will be more likely to achieve a healthy gestational weight gain during pregnancy and better maintain their pre-pregnancy weight post pregnancy. Weight-gain that is above the IOM guidelines is considered excessive gestational weight-gain.

The primary objectives of the study are to:i)Compare the differences in gestational weight gain and weight retention at 12 months post birth of participants in the health coaching and information only armsii)Understand the acceptability and experiences of telephone-based coaching amongst pregnant women and antenatal service providers.

As secondary objectives, the study will:iii)Compare changes in diet (fruit, vegetable, fast food and sweetened drink intake)iv)Assess the predictors of service participation and retentionv)Explore service usage patterns such as length of calls and preferred timevi)Assess confidence to changevii)Provide recommendations for program improvement.

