**Fig. 1 Fig1:**
[figure not shown]
Study flowchart

Randomisation of hospitals, stratified by metropolitan and rural regions, will be undertaken using Microsoft Excel 2010© randomisation generator. Two rural hospitals were combined into one unit for randomisation because they are in the same Local Health District and their aggregated total number of births in 2012 was similar to the total of the other rural hospital in the study. Face-to-face training will be provided, by members of the research team, to the midwives and medical officers at each site to describe the study and the program. The hospitals will develop their own processes to integrate the GHiP referral into the first antenatal appointment for pregnant women. As part of this process, hospitals in both arms will be required to include initial discussion on the importance of healthy gestational weight gain, the setting of a target weight-gain range for the woman’s pregnancy (as per IOM recommendations), screening of the woman for exclusion criteria and recruitment of women following consent.

Health coaches (primarily dieticians and exercise physiologists) delivering GHiP will be provided with a day’s face-to-face training by clinical experts in dietetics and maternity care, in addition to their usual training. A list of online resources to support the pregnant women will also be available to all health coaches. The clinical experts will also be available for further consultation as required.

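### The stated 80% power for a 3 kg difference is not delivered by a test that respects the four randomised units

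*Protocol article*

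**What the plan says.** The Sample size section gives a total of 710 women, of whom 462 are metropolitan and 248 rural. It states the target as "to detect a difference of 3 kgs in gestational weight gain between intervention and control groups", with 80% power, and expects to lose 60% of the coaching arm and 30% of the information only arm. The basis is described as follows: "The sample size has been calculated using previous reports of weight gain during pregnancy". The article states no SD, significance level, ICC, design effect or number of clusters for this calculation.

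Allocation is by hospital (Study design). The text after Fig. 1 reads "Randomisation of hospitals, stratified by metropolitan and rural regions" and adds that two of the three rural hospitals form one unit for this purpose. With the two metropolitan hospitals (Study setting), that makes four randomised units, two per region. Stratification therefore implies one unit per arm in each region.

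Under Data analysis, the primary comparison of weight change is an independent samples t-test. Hospital clusters enter only the secondary model for predictors of weight gain.

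**The concern.** Power in a cluster randomised trial is limited by the number of randomised units as well as by the number of women. With four units, the between-unit variation has to be estimated from 2 degrees of freedom, or 1 if region is kept. The critical value then rises from 1.96 to 4.30 or 12.7. No number of women within the same four units changes that. An unqualified 80% invites two misreadings: that a null result argues against a 3 kg effect, and that a positive result came from an adequately powered comparison. This matters because the Discussion expects the findings to inform rapid extension of the service to other hospitals.

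**Working it through.** **Inputs from the article.** Difference 3 kg; power 80%; 710 women (462 metropolitan, 248 rural); losses 60% and 30%; four randomised units, two per region.

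**Assumptions, not in the article.** Two-sided alpha 0.05; 355 women per arm; each region's women split equally between its two units; SD 6 kg (range 4–10); ICC 0 to 0.05.

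**1. Reproducing the 80%.** Women with data: 355 × 0.4 = 142 and 355 × 0.7 = 248.5. Ignoring clusters, SE = SD × √(1/142 + 1/248.5) = 0.105 × SD. For 80% power, 3/SE must equal 1.96 + 0.84 = 2.80.
- All 710 women, no clustering: SD = 3/(2.80 × 0.1052) = 10.2 kg. At SD 6 the same calculation gives 99.7% power.
- All 710 women, SD 6, with clustering: the unclustered requirement is 2 × 2.80² × 36/9 × (1/0.4 + 1/0.7) ≈ 247 recruited. The ratio 710/247 is a design effect of 2.9. With 390.5/4 ≈ 98 women with data per unit, ICC ≈ (2.88 − 1)/96.6 ≈ 0.019.

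The figure can be reproduced in more than one way, and the article does not say which was used.

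**2. Degrees of freedom.** Four unit means less two arm means leave 2 df (critical t 4.30). Keeping region costs one more, leaving 1 df (critical t 12.7).

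**3. A result that needs no SD.** If the stated 80% is a woman-level figure, the noncentrality is 2.80. Putting 2.80 into the noncentral t gives 35% with 2 df and 17% with 1 df, at ICC 0. If a design effect was already included, the noncentrality is 2.80 at the ICC that was built in, so the same 35% and 17% apply at that ICC.

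**4. With an assumed SD of 6 kg and all 710 women.** Women with data per unit (m): 231 × 0.4 = 92.4; 124 × 0.4 = 49.6; 231 × 0.7 = 161.7; 124 × 0.7 = 86.8. Comparing averages of unit means:

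variance = ¼ × Σ[ICC × SD² + (1 − ICC) × SD²/m]

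At ICC 0.02 this is ¼ × [4 × 0.02 × 36 + 0.98 × 36 × 0.0487] = 1.15, so SE = 1.07 kg. The expected 95% CI half-width with 2 df is 4.30 × 1.07 ≈ 4.6 kg.

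| ICC | SE (kg) | 3/SE | Power, 2 df | Power, 1 df | Half-width, 2 df (kg) |
|---|---|---|---|---|---|
| 0 | 0.66 | 4.53 | 65% | 28% | 2.85 |
| 0.01 | 0.89 | 3.37 | 45% | 21% | 3.83 |
| 0.02 | 1.07 | 2.80 | 35% | 17% | 4.61 |
| 0.05 | 1.49 | 2.02 | 22% | 13% | 6.41 |

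The 2 df figures ignore region, so any metropolitan–rural difference in mean gain would reduce them further.

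**5. Sensitivity to the SD.** With 2 df and ICC 0, power is 90% at SD 4, 84% at 4.5, 78% at 5 and 34% at 10. At SD 4 it falls to 73% at ICC 0.01. With 1 df it is at most about 41% for any SD from 4 to 10 kg.

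**6. The planned test.** The woman-level t-test does not rescue the figure. Simulated with these unit sizes, its two-sided type I error is about 16%, 25% and 42% at ICC 0.01, 0.02 and 0.05.

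**The case against.** The article condenses a fuller protocol, and omitting the SD, ICC and design effect is normal in that format. The authors plainly knew that the design was clustered: they name it as such and put hospital effects in the secondary model. A reader might infer from the silence that clustering was left out of the sample-size calculation, or that 710 was derived from the 177 healthy-weight women alone (which fits an SD of about 5.1 kg). The documents support neither inference, because 710 also fits all women at SD 10.2, or SD 6 with an ICC of about 0.019. This part of the objection stands. It does not answer the concern, since a design effect inflates the variance but leaves the degrees of freedom at 1 or 2.

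A second objection is that at an ICC of exactly zero the woman-level test is valid and has ample power. That is true, but nothing in the article supports a zero ICC. Its Discussion expects recruitment to vary with local leadership, individual midwives and the organisation of care.

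A third is that the size of the shortfall depends on assumed SDs and ICCs and spans a wide range. That also stands, and it is why ranges are given here. The SD-free result in step 3 does not depend on the SD.

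**Conclusion.** The concern holds. Four randomised units and an unqualified 80% power for 3 kg do not go together. A test that allows for a non-zero ICC has roughly 35% power (2 df) or 17% (1 df) if the stated figure is a woman-level one. At an assumed SD of 6 kg and ICC 0 to 0.05, with all 710 women, it has 65% down to 22% (2 df) or 28% down to 13% (1 df).

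A reader might go further and infer that no plausible inputs could give 80%. That is too strong: the 2 df test gets there if the SD is below about 5 kg and the ICC is essentially zero. Only the 1 df test, which matches the stated stratification, falls short across the whole SD range of 4 to 10 kg.

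The count of four units and the degrees of freedom follow from the article. The SD, ICC, significance level, equal arms and equal split within region are assumptions.

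**What to change.** In the Sample size section, remove the 80% claim. Replace it with the power, or the expected 95% CI half-width, for four randomised units. State the SD, ICC, significance level, numbers with data and degrees of freedom used. As an illustration, at SD 6 kg, ICC 0.02 and 2 df the half-width is about ±4.6 kg, wider than the 3 kg target. Add a sentence saying that a null result does not exclude a 3 kg effect.

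This is a change of text. It needs no additional women or hospitals. The cost is a much less favourable stated figure.

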### Study design

This study employs a pragmatic stratified cluster randomised design [31] with stratification by healthy weight and overweight/obese pre pregnancy BMI.

Pregnant women in the study will be allocated to either the information only or health coaching group based on the hospital where they present for antenatal care (Fig. 1). This design was selected to obtain results that can be generalised with high external validity and utility in the real world setting. In this study, the trial environment and processes will be as close as possible to how the program would be rolled out if effective. A range of hospitals in both metropolitan and rural settings, of different sizes and maternity service delivery levels have been chosen to test the scalability of the intervention across the state.

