### The interventions

#### Coaching arm

Women in the coaching arm will be enrolled in a full coaching program comprising of up to 10 calls by university qualified coaches (8 during pregnancy and 2 after birth). Health coaches, using behaviour change informed coaching techniques, will in their first call confirm and discuss the woman’s weight range target according to the IOM guidelines, and develop personally relevant lifestyle change goals and actions for participants to achieve their target weight range. In subsequent coaching calls health coaches will ensure that no conditions have presented in the pregnancy that may require medical clearance or adapted advice, revisit goals and revise them accordingly with the participant, help maintain motivation, discuss strategies for overcoming barriers and prevent relapse of healthy behaviours. Health coaches are guided by a range of national and international guidelines for nutrition, exercise and weight-gain targets for pregnancy. The timing of calls is designed to be flexible based on participant preferences and will generally last between 15 and 25 min. A recommended schedule for the pregnancy coaching calls will be used; three in the first 3 weeks, followed by a call every 2–4 weeks until the end of the pregnancy with two calls post birth.

In addition, participants in the health coaching group will be provided with supportive materials including pregnancy specific factsheets on healthy eating, exercise and the benefits of healthy weight-gain during pregnancy and a general information booklet and diary for setting and tracking health goals. Women will receive usual care from their maternity clinicians during the trial with the exception to setting their weight-gain range target and general advice about gestational weight gain at their first antenatal visit with their midwife.

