### Data analysis

#### Primary objectives

All quantitative data analysis will be based on intention to treat principles. Differences between the two study groups in self-reported weight change from pre-pregnancy weight to weight at 36 weeks gestation and 12 months post birth will be tested using the independent samples *t*-test. The proportions of pregnant women who achieve weight gain within the recommended range and those who return to their pre-pregnancy weight 12 months post birth will be analysed using the *X*^2^ test. The adjusted means of the BMI outcomes at 36 weeks gestation and follow up by BMI category will be compared with the pre pregnancy BMI.

Interview data will be analysed using the thematic analysis approach. The transcribed interviews will be coded by the researchers and if there is a disagreement in the classification of interview responses, the researchers will convene as a group to discuss the discrepancies and revise coding categories if needed. Once agreement is reached, themes and sub-themes will be extracted from the data. Data from the interviews will inform the provision of recommendations for program improvement.

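### Intention to treat is claimed, but women already allocated are excluded from the study for conditions that develop later, and nothing keeps them in outcome follow-up

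*Protocol article*

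**What the plan says.** Data analysis, Primary objectives: "All quantitative data analysis will be based on intention to treat principles".

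Study design: women are "allocated to either the information only or health coaching group based on the hospital where they present for antenatal care". The arm is therefore fixed before a woman is screened, consented or called.

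Medical conditions, Table 1: one column covers conditions that develop during the study, and its upper row lists those that lead to exclusion from the study. They include fetal death, small for dates, preterm birth, rupture of membranes before 36 weeks and placental problems. The text after the table lets a medical clearance review end in exclusion from the trial.

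Sample size: the expected attrition is 60 % in the coaching arm and 30 % in the information only arm. Both figures include women "who start the study and go on to develop conditions during pregnancy that exclude them from further participation", a share put at no more than 15 % for the two arms together.

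Coaching arm: "In subsequent coaching calls health coaches will ensure that no conditions have presented in the pregnancy that may require medical clearance". The same sentence extends the check to conditions that call for a change in advice. The Information only arm section describes a single session and no later check.

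Participants: membership of the study requires "signed consent forms and verbal consent provided at first coaching call".

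Data collection, Quantitative: a research assistant contacts coaching women who stop the program without withdrawing from the study, to obtain endpoint data. Women excluded for a medical condition are not mentioned.

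**The concern.** Intention to treat needs every allocated woman to stay in her arm whatever happens afterwards. A rule that takes women out of the study for later events works against that. It matters more when the event may be tied to the outcome. The Background links gestational weight gain to infants who are large for gestational age, and says the recommended ranges rest on least risk of adverse perinatal outcomes. A link between low weight gain and small for dates is therefore plausible, and coaching aims to change weight gain.

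If women are removed at different rates, or for different reasons, in the two arms, the women left are no longer comparable. Neither the planned t-test nor a model with hospital effects corrects for that. Both primary weight outcomes, at 36 weeks and at 12 months after birth, are exposed.

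Two related points need tidying. Women lost between written consent and the first call could vanish from the count, because verbal consent at that call is part of the definition of a participant. And small for dates appears twice in the same column of Table 1, once leading to exclusion ("Small for dates (<10th centile") and once to medical clearance ("Fetal size small for dates").

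**Working it through.** **1. The plan's own figure.** Inputs, both from Sample size: up to 15 %, and 710 women. 0.15 × 710 = 106.5, so up to about 106 women. The article does not give the split by arm. If it is 1:1 (assumption), each arm has 355 women and 0.15 × 355 = 53.25, about 53 per arm.

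**2. Place within expected attrition.** At the 15 % ceiling, other losses are 60 − 15 = 45 points in coaching and 30 − 15 = 15 points in information only. The condition-related losses are the same in both arms on the plan's figure. The gap between the arms lies in the other losses, which the plan puts down to perceived burden of coaching.

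**3. Who is followed up.** The Data collection section separates stopping coaching from withdrawing from the study, and gives endpoint contact only to women who have stopped coaching but not withdrawn. Table 1 and the clearance text speak of exclusion from the study or trial. Followed as written, these rules put women with later conditions outside that provision.

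**4. Size of the possible bias.** Suppose there is no true effect. Let p_C and p_I be the shares removed in the coaching and information only arms. Let d be the mean weight gain of removed women minus that of women kept, the same in both arms (assumption). The mean among women kept in an arm is the full mean minus p × d. The comparison of women kept is therefore off by

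bias = (p_C − p_I) × d in size, with the direction set by the sign of d.

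The article gives neither d nor separate removal shares, so the table shows a range (kg):

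| d (assumed) | 15 % v 15 % | 15 % v 10 % | 15 % v 5 % | 15 % v 0 % |
|---|---|---|---|---|
| 1 kg | 0 | 0.05 | 0.10 | 0.15 |
| 3 kg | 0 | 0.15 | 0.30 | 0.45 |
| 5 kg | 0 | 0.25 | 0.50 | 0.75 |

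Example: (0.15 − 0) × 3 = 0.45 kg. Against the 3 kg difference the trial is sized to detect, that is 0.45 / 3 = 15 %. (The 3 kg used for d is a separate assumption that happens to equal the target.) The zero column needs removed women to be alike in both arms, as well as equally many.

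**The case against.** The best defence is that the exclusions concern the intervention. Table 1 exists for safety, and the conditions were reviewed for whether a woman can safely change her diet or activity. Exclusion from further participation, the phrase in Sample size, could mean that the program stops. Allowing for losses in a sample size does not breach intention to treat, and definitions of analysis sets are commonly left to a fuller document. Much of this stands. It rules out the claim that the analysis will certainly break intention to treat. It does not remove the conflict, because Table 1 and the clearance text say study and trial, and the article itself treats leaving the program and leaving the study as different things.

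A reader might infer that the exclusions and the consent step apply unequally to the arms. The documents do not say so. The 15 % is given for both arms together. Both arms have a first call, so unequal refusal there is only a possibility. Unequal detection of later conditions is an inference from where the checks are described. The quoted check concerns medical clearance and adapted advice and says nothing about removal from analysis. Many of the listed events are overt, and both arms receive usual maternity care. The inference is strongest for less obvious conditions and for clearance reviews that end in exclusion.

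A reader might also blame the 60 % versus 30 % attrition on these exclusions. The plan attributes the extra loss to coaching burden.

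Finally, not every listed event is an avoidable exclusion. When a pregnancy ends before 36 weeks, no 36-week weight can exist. That is a question of how the outcome is defined. Multiple pregnancy may be an eligibility matter, since singleton pregnancy is an entry criterion. The two small-for-dates entries may be meant as grades, as only one carries a threshold, but the table does not say so.

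**Conclusion.** The point holds as a conflict in the text. Intention to treat is claimed, study-level exclusion after allocation is prescribed for up to about 106 of 710 women, and no provision keeps them in outcome follow-up. That some of the conditions are related to weight gain is plausible, and unequal detection is a risk. Neither is established by the documents.

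The resulting bias ranges from zero, when removal is alike in both arms, to about 0.45 kg at 15 % versus 0 % with an assumed 3 kg difference. The latter is an extreme case and modest against the 3 kg target. The direction is unknown. Losses at the first call are not included and cannot be sized from the article.

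Should-fix: the possible bias is limited, but the text decides who enters the primary comparison, and the remedy is cheap.

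**What to change.** - State that stopping the intervention and leaving the study are different. Women who develop a Table 1 condition stay in their hospital's arm for analysis, whatever happens to their coaching. This leaves all clinical decisions untouched.
- Collect their 36-week weight where they are still pregnant, and their 12-month weight, unless they withdraw consent.
- State how births before 36 weeks are handled for the 36-week outcome.
- Define the analysis set from written consent, so that losses before or at the first call are visible. This does not remove selection at recruitment, because the hospital's allocation is already fixed when written consent is sought.
- Report by arm, with reasons, exclusions for later conditions and losses between written consent and the first call.
- Have the clinical team reconcile the two small-for-dates entries in Table 1.

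Cost: changes to the wording of the analysis set and Table 1, and some extra calls by the research assistant who already follows women who stop coaching. The written consent must cover outcome contact for women who never take the first call. Their baseline data may also be incomplete, since in the coaching arm the health coach collects them.
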